### Interventions

#### Usual care

Usual care includes treatment/follow-up by the oncologist and the GP after completion of the first therapy, according to the usual procedure (usually this is done quarterly during the first year after treatment):

a) Follow-up with regard to course of illness

b) Treatment of delayed adverse effects of therapy

c) Rehabilitation, support directly organised by the oncologist/GP

The rehabilitation (i.e. physiotherapy, physical movement/sports, nutritional advice) and the psychosocial support/counselling (i.e. provided by the Swiss Cancer League and/or psycho-oncologists) correspond with the individual needs of the patients and will, as is current practice, be arranged either by initiative of the patient and/or referral by the medical practitioner. There are no restrictions regarding rehabilitation measures and support. A standardisation of 'usual care' to avoid a bias would contradict the individual needs of the patient.

## Case Management

Table 1 shows a summary of the procedure and content of case management (table 1).

**Table 1 T1:** Summary of the procedure and content of case management.

Procedure	Method	Content
1st consultation	Assessment of needs: setting goals/measures according to standardised procedure (CM control system/self-management) Provision of information Ambulant rehabilitation Approach: Motivational counselling Resource-oriented Empathic conduct	Get to know patient, establish relationship, clinical recording of overall situation: symptoms, side effects of therapies, psychosocial situation and distress, impairment of quality of life. If required by patient: clarification on rehabilitation offered, contact person in case of queries and problems

2nd consultation 3rd consultation	Counselling/Instruction Guidance based on targets &measures Approach as above 'Define task/needs'	Develop 'program' in collaboration with patient. Counselling: dealing with symptoms etc. Arrange a therapists, services, e.g. Swiss Cancer League, via GP/oncologist: physiotherapy, nutritional advice, psycho-oncologist, if patient is unable to organise himself. Contact person in case of queries and problems

**Telephone follow-up **at least once per month for approx. 30 minutes during the first 6 months, afterwards reduction if needed. Availability of rehabilitation coaches if required/office hours	Evaluation, possibly new goals, planning Approach as above	Summarising of outcomes, poss. summarise reports of therapists for patient, GP/oncologist. Counselling to encourage self- management. Contact person in case of queries/problems

4th consultation	Evaluation	Concluding interview

The case manager (rehabilitation coach) informs the patient about the appropriate therapeutically and supportive measures and establishes the necessary. The rehabilitation coach offers supplementary patient-orientated advice and instruction and thus encourages self-management. In this way, the belief in self-advocacy through the accomplishment of a more positive mental outlook can be strengthened. The patient is allocated to a rehabilitation coach who will advise and guide the patients during the rehabilitation phase, and, if necessary, during the chronic phase of the illness. The 'motivational interviewing' [22] with the aim to influence behavioural changes by communicating in an accepting and empathic way, serves as basis for communication with patients. The role of the rehabilitation coach is assumed by an experienced, qualified nurse with additional training in oncology care and further training in case management, hired by the Institute of General Practice and Health Services Research, Zurich. For five days and with ongoing weekly training the rehabilitation coaches were prepared and supported in the requirements during a specially designed training program. The equivalent of 120% employment percentage has been made available for the trial to be distributed among four rehabilitation coaches. The program director or research associates/study nurse will not coach the patients.

The intervention with case management lasts for one year. If the patient no longer requires care, the intervention will be concluded earlier.

### Intervention in control group

All patients receive the usual care and counselling after completion of the therapy, as described under the section 'usual care'.

### Measurements

#### Patient characteristics

Demographics include age, gender, education, race/ethnicity, family status, employment status

Medical characteristics include diagnosis and therapies, time since cancer diagnosis, other diagnosis and therapies, supportive therapies.

### Outcome measures

To determine the health-related quality of life (primary outcome), the general questionnaire FACT G version 4 is used. It contains a summary of 27 items divided into four primary focal points relating to quality of life.

To measure secondary outcomes such as ability to work, the days of sick leave will be recorded at work, as well as the help needed with daily chores. The direct correlation between self-management and perceived self-efficacy is measured with the Jerusalem & Schwarzer questionnaire [23]. The satisfaction of patients with the care received is measured using the Patient Assessment of Chronic Illness Care (PACIC 5-A), which has been developed to assess congruency of provided health care to the Chronic Care Model (CCM). Table 2 gives an overview of the measuring tools for the primary and secondary outcomes (table 2). Data is collected at the beginning of the trial, and after 3, 6 and 12 months.

**Table 2 T2:** Overview of measuring tools/measuring time

Outcomes	Measuring tool	Point in time
**Primary Outcome** Quality of life	FACT G	Months 0, 3, 6, 12

**Secondary Outcomes**		Months
Employability	Questionnaire	0, 3, 6, 12
Self - efficacy Unplanned consultations (GP/oncologist, specialist) and hospitalisation Satisfaction with medical care Type, number of rehabilitation measures	Questionnaire self-efficacy expectation by Jerusalem & Schwarzer Number of consultations/rehabilitation- and support measures Questionnaire PACIC 5-A Questionnaire- patient logbook	

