## Methods

### Objectives

The primary goal of the trial is to assess whether the quality of life of cancer patients with usual care plus case management is significantly better compared to usual care alone one year after a first therapy.

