### Sample size

The power calculation was based on the following data: mean value in primary outcome (FACT) 22.7, a variation of 3.0 units in the FACT-score is considered clinically relevant and is thus imputed as minimal difference (effect) to be achieved. The standard deviation of FACT is 5.4 according to literature; the level of significance was set at 0.05, also a power at 0.8. The power analysis revealed a sample size of 102 patients. Assuming a drop-out rate of 30% due to the severely ill patient population, 132 patients would need to be enrolled. The calculation of the sample size was done with the aid of Southwest Oncology Group computers.

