### Statistical analyses

Continuous primary and secondary outcomes will be checked by the Shapiro-Wilk test for normality distribution and data are expressed by means with standard deviations and medians with interquartile range as appropriate. Categorical variables will be expressed as percentages. Primary and secondary outcomes will be compared between groups to investigate the effect of the case management on oncology rehabilitation using parametric or non-parametric tests as appropriate. Categorical outcomes will be analysed by Chi Square tests. To control for any imbalance between groups multiple regression analysis will be used and measures that show any difference in baseline characteristics will be included into the model as potential confounders.

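### The stated primary comparison of FACT-G gives the 3- and 6-month scores no role and baseline only a conditional one, which costs precision and leaves it open to drop-out bias

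*Protocol article*

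**What the plan says.** All of the following is in the protocol article.

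- Objectives: the question is whether quality of life under "usual care plus case management is significantly better compared to usual care alone one year after a first therapy".
- Outcome measures and Table 2: FACT-G is the primary outcome. "Data is collected at the beginning of the trial, and after 3, 6 and 12 months".
- Statistical analyses: "Primary and secondary outcomes will be compared between groups to investigate the effect of the case management on oncology rehabilitation using parametric or non-parametric tests". Regression is reserved for imbalance: "measures that show any difference in baseline characteristics will be included into the model as potential confounders".
- Sample size: "a variation of 3.0 units in the FACT-score is considered clinically relevant and is thus imputed as minimal difference (effect) to be achieved". An SD of 5.4 is taken from published sources. The evaluable total is 102. "Assuming a drop-out rate of 30% due to the severely ill patient population", enrolment is raised to 132.
- Exclusion from study: a patient who relapses or progresses, with worsening quality of life, leaves the trial.
- Patient informed consent: on study discontinuation the material is destroyed, or the patient is asked to agree to its use.

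The Statistical analyses section names neither month 12 nor complete cases. It describes no use of the 3- and 6-month scores in the primary comparison.

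**The concern.** The trial measures its primary outcome four times and expects to lose almost a third of its patients for reasons connected with illness, and so plausibly with quality of life. A group test on 12-month scores draws nothing from a patient who answered at months 0, 3 and 6 and then left. It also ignores baseline FACT-G, usually a strong predictor of the 12-month score, unless the arms happen to differ on it.

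Two things are at stake. One is precision, in a trial that reports recruitment difficulty. The other is bias: if those who leave had lower earlier scores, the patients with a final score are a selected group, and a plain comparison of them does not correct for that selection.

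**Working it through.** **Inputs from the article.** Difference 3.0, SD 5.4, significance level 0.05, power 0.80, drop-out 30%, enrolment 132. These are taken at face value.

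**Assumed, because the article does not give them.** A two-sided test, 1:1 allocation (suggested by block sizes 2 and 4), between-visit correlation 0.5 to 0.7, and the form and steepness of the drop-out relation.

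**1. The plan's own figure.** n per arm = 2 × (1.96 + 0.842)² × 5.4² / 3.0² = 50.9, rounded up to 51, so 102 in total. This reproduces.

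**2. Final scores left.** 132 × 0.70 = 92.4, or 46.2 per arm. (132 is close to 102 × 1.3 = 132.6, whereas 102 / 0.70 = 145.7. That is a separate matter, but it makes precision scarcer.)

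**3. Precision of the two-group test.** SE = 5.4 × √(2/46.2) = 1.12. Power = Φ(3.0/1.12 − 1.96) = Φ(0.71) = 76%.

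**4. Precision with baseline FACT-G always in the model.** SE is multiplied by √(1 − r²).
- r = 0.5: 1.12 × 0.866 = 0.97, 13% smaller.
- r = 0.7: 1.12 × 0.714 = 0.80, 29% smaller.

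**5. What months 3 and 6 add to precision.** In simulated trials of 132 patients with about 30% lost, the empirical SEs were:

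| Correlation | Two-group test | Completers, baseline-adjusted | Repeated measures |
|---|---|---|---|
| 0.5 | 1.05-1.15 | 0.95-1.03 | 0.94-1.03 |
| 0.7 | 1.05-1.11 | 0.79-0.84 | 0.77-0.83 |

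The second and third methods almost coincide, so the gain comes from baseline.

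**6. Bias when drop-out depends on the last observed score** (true difference 3.0; the log-odds of leaving rise by the stated amount per SD of lower score):

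| Mechanism | Two-group test | Completers, baseline-adjusted | Repeated measures |
|---|---|---|---|
| Unrelated to scores | 2.95-3.02 | 2.97-3.01 | 2.98-3.02 |
| Both arms, 1.0 | 2.72-2.89 | 2.88-2.97 | 2.99-3.02 |
| Control arm only, 1.5 | 1.34-1.78 | 2.54-2.64 | 3.00-3.01 |
| Intervention arm only, 1.5 | 4.06-4.54 | 3.23-3.36 | 2.98-3.02 |

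In the table patients can leave before month 3. A separate set of runs, with loss only after months 3 and 6, gave 2.9 when both arms behaved alike. When low scorers left mainly from one arm it gave 1.84-2.18 or 3.65-3.91, which is 0.7 to 1.2 away from 3.0. With no true effect the one-arm mechanism gave a spurious 0.8-1.2. With no true effect and the same mechanism in both arms, symmetry makes the bias zero.

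**7. If drop-out depends on the score not yet observed**, in one arm only: repeated measures gave 2.3-2.6 or 3.4-3.6, against 1.7-1.8 or 4.1-4.2 for the two-group test. With no true effect, repeated measures was off by 0.4-0.7. The model reduces this bias but does not remove it.

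**The case against.** The strongest reply is that this is a condensed article. It is silent on missing data, which a full protocol or analysis plan may settle, and a group test or regression can follow multiple imputation from months 0, 3 and 6. That stands in part. A reader might infer that the plan commits itself to discarding everyone without a final score, but the text does not say so. That reading is pieced together from the one-year objective, the kind of test named, and enrolment inflated as if drop-outs add nothing. What survives is narrower: the article does state a primary method, and that method makes baseline FACT-G conditional on chance imbalance and gives two planned assessments of the primary outcome no role.

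Three further objections also hold.

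- A reader might infer a large bias. That needs drop-out to depend on scores in one arm only, which no section states. The reasons the article gives for leaving apply to both arms. Unequal loss is conceivable, since only the intervention arm has regular coach contact, but it is an assumption, and its assumed steepness drives the size.
- A reader might credit the precision gain to the unused 3- and 6-month scores. Step 5 shows that they add very little to precision; their value is against bias.
- A reader might take the repeated-measures model as a cure. Exit at relapse or progression may come before the worse score is recorded, so step 7 may be nearer the truth than step 6. Patients with no post-baseline score stay outside the model too. And if the discontinuation rule in the consent section refers to individual patients, some earlier scores may not be available.

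**Conclusion.** The point holds in this limited form. The stated comparison is less efficient than the trial's own data allow: SE about 1.1, against about 0.95-1.0 at correlation 0.5 or 0.8 at 0.7. Nearly all of the difference is due to baseline adjustment. Read as a test on available 12-month scores, it is also exposed to bias if drop-out depends on earlier scores. That bias is small, about 2.8-2.9 for a true 3.0 (2.7 in the least favourable run), and nil when there is no effect, if the mechanism is alike in both arms. In an assumed one-arm mechanism it is roughly 0.7-1.2 units in either direction, reaching 1.7 with the steeper relation. The documents do not establish that scenario, so it shows vulnerability and is not a forecast. All of these sizes rest on the assumed correlations and drop-out relations.

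**What to change.** - Make the primary analysis a mixed model for repeated measures on FACT-G at months 3, 6 and 12. Include arm, visit, arm-by-visit, baseline FACT-G, baseline-by-visit and tumour stratum, with unstructured covariance. Baseline FACT-G enters whether or not the arms differ on it.
- Name the month-12 arm contrast as the single primary test. Include every randomised patient with any post-baseline score, in the randomised arm.
- Because exit at relapse may depend on unobserved scores, add one delta-adjusted sensitivity analysis in which scores after drop-out are worse than the model predicts.
- Reconcile the discontinuation wording under Patient informed consent with this analysis. State whether it concerns the individual patient, and how agreement to use scores already given is obtained.

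The cost is analysis wording, a little programming, and asking patients who leave for that agreement. No additional assessments are needed.

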### Sample size

The power calculation was based on the following data: mean value in primary outcome (FACT) 22.7, a variation of 3.0 units in the FACT-score is considered clinically relevant and is thus imputed as minimal difference (effect) to be achieved. The standard deviation of FACT is 5.4 according to literature; the level of significance was set at 0.05, also a power at 0.8. The power analysis revealed a sample size of 102 patients. Assuming a drop-out rate of 30% due to the severely ill patient population, 132 patients would need to be enrolled. The calculation of the sample size was done with the aid of Southwest Oncology Group computers.

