### Randomisation

Treatment allocation will be done by random permutation within blocks with block sizes of 2 and 4. In addition to the block randomization allocation will be stratified according to the type of carcinoma (breast carcinoma, colon carcinoma, Hodgkin and Non Hodgkin lymphoma and one group with "other tumor types") thus allowing for an even distribution of the intervention through the most common expected tumor types with regard to the participating centres various diagnoses. As the size of the participating centres is not necessarily related to the contribution of the participating centres regarding the patient recruitment we will not perform a randomisation stratified by centre. The randomisation is done independently of centres, rehabilitation coaches and the study nurse. The study nurse is responsible for providing patients with detailed information; additionally, they are in charge of the assessment.

The randomisation is performed with STATA statistic program. The relevant information is only accessible to an employee of the Institute of General Practice and Health Services Research who is not involved in the trial. After the inclusion of a patient in the trial and the baseline assessment, the study nurse receives information concerning the allocation of patients to the intervention or control arm by sequentially numbered opaque sealed envelopes. Therefore, the blinding regarding the allocation is guaranteed.

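### The sample size rests on an unnamed FACT score whose mean and SD look like those of one domain, so 80% power is not shown for the 27-item FACT-G named as primary outcome

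*Protocol article*

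**What the plan says.** The Objectives section sets quality of life at one year as the primary question. The Outcome measures section names the instrument: "To determine the health-related quality of life (primary outcome), the general questionnaire FACT G version 4 is used". It describes the structure: "It contains a summary of 27 items divided into four primary focal points relating to quality of life". Table 2 lists FACT-G against the primary outcome. None of these places singles out a domain, so the natural reading is that the whole questionnaire is the endpoint.

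The Sample size section gives the power inputs for a score called only FACT: "mean value in primary outcome (FACT) 22.7, a variation of 3.0 units in the FACT-score is considered clinically relevant". It adds "The standard deviation of FACT is 5.4 according to literature" and "the level of significance was set at 0.05, also a power at 0.8". From these it derives 102 patients. It does not say whether the score is the total, a domain or a rescaled score, and it gives no score range. The item scoring appears nowhere in the article.

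**The concern.** A sample size calculation supports an endpoint only if its SD and target difference belong to that endpoint's score. Here a mean of 22.7 and an SD of 5.4 are hard to reconcile with the sum of 27 questionnaire items, but they are ordinary values for a scale of about seven items. If the figures come from one domain, two things are unsupported for the total: its SD, which will be larger than that of any single domain if the domains are positively correlated, and the claim that 3.0 points is a relevant difference on it. The ratio 3.0/5.4 is the only basis for 102 patients, so the planned size would then have no stated justification for the primary endpoint.

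**Working it through.** **Inputs from the protocol.** Difference 3.0, SD 5.4, alpha 0.05, power 0.8, mean 22.7 (Sample size); 27 items, four domains (Outcome measures). Equal allocation is inferred from two arms and "random permutation within blocks with block sizes of 2 and 4" (Randomisation). Two-sided testing is inferred because it reproduces the stated figure.

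**1. The protocol's own figure.** n per arm = 2 × (1.960 + 0.842)² × (5.4/3.0)² = 50.9, so 51 per arm and 102 in total. Power at 51 per arm is 0.801 by the normal approximation and 0.793 by the t-test. A one-sided test would give 41 per arm, 82 in total, which does not match. The stated 102 is reproduced.

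**2. Does the mean fit a 27-item total?** 22.7/27 = 0.84 points per item. The item scoring has to be assumed:

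- Items 0 to 4, summed: the maximum is 27 × 4 = 108, and 22.7/108 = 21%. Mean plus two SDs is 22.7 + 10.8 = 33.5, or 31% of the maximum.
- Items 1 to 5, summed: the lowest possible total is 27, so a mean of 22.7 is impossible.
- A 7-item domain scored 0 to 4: the maximum is 28, and 22.7/28 = 81%.
- A 6-item domain scored 0 to 4: the maximum is 24, and 22.7/24 = 95%, a much tighter fit.

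Reading 21% as poor quality of life also assumes that higher scores are better. The SD check below does not depend on that.

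**3. Does the SD fit a 27-item total?** For k items with a common item SD s and average inter-item correlation r, SD of the sum = s × √(k + k(k − 1)r). Setting this to 5.4 and solving for s (r is assumed):

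| Items k | r = 0.2 | r = 0.3 |
|---|---|---|
| 27 | s = 0.42 | s = 0.35 |
| 7 | s = 1.38 | s = 1.22 |

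On a five-point item, an SD of 0.35 to 0.42 means that nearly all patients give the same answer. Values of 1.2 to 1.4 are ordinary.

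**4. What follows if 3.0 points is kept on the total.** Assume that each of the four domains has SD 5.4 and that every pair has correlation ρ. Then SD of the total = 5.4 × √(4 + 12ρ). With 51 per arm and a two-sided t-test, the detectable difference is 0.560 × SD:

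| ρ | SD of total | Power for 3.0 points | Difference detectable at 80% power |
|---|---|---|---|
| 0 | 10.8 | 28% | 6.1 |
| 0.5 | 17.1 | 14% | 9.6 |
| 1 | 21.6 | 11% | 12.1 |

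**5. What follows if the target grows with the scale.** Power depends only on difference/SD. The stated ratio is 3.0/5.4 = 0.556, so power stays at about 80% if the relevant difference on the total is 0.556 SD: 0.556 × 10.8 = 6.0 points, 0.556 × 15 = 8.3 points, or 0.556 × 21.6 = 12.0 points. In the model of step 4, a 3.0-point shift in all four domains is 4 × 3.0 = 12 points on the total. That gives about 80% power at ρ = 1 and more at any lower correlation (94% at ρ = 0.5).

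**The case against.** The strongest reply has four parts.

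- **The calculation is right.** The stated inputs give 102. This stands in full: the problem is which score the inputs describe, not the arithmetic.
- **The mismatch is inferred.** The article gives no item scoring, no score range and no other FACT-G mean or SD. The patients must also show raised distress and a need for rehabilitation, and the Sample size section calls them severely ill, so a low mean is not excluded on clinical grounds alone. This stands as a limit on certainty. It does not remove the doubt, because the SD points the same way without any judgement about how ill the patients are.
- **Low power does not follow automatically.** A reader might infer that the trial has only 11% to 28% power, or that the 80% figure is simply false. The documents do not support either reading. That range keeps 3.0 points on the total while enlarging only the SD, and step 5 shows that a proportionate target restores about 80%. What remains is that the Sample size section fixes 3.0 units as the effect to be achieved and justifies no larger difference.
- **The article is condensed.** The scoring and the source of the SD may stand in a fuller protocol. That would explain missing detail. It does not settle how the stated inputs relate to the stated endpoint, since both appear here and do not visibly match.

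A reader might also infer that several domain scores are open to selection as the endpoint. The article plans no domain-level tests, so that reading has no support.

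**Conclusion.** The point holds in a limited form. The protocol names the whole FACT-G as primary outcome and takes its power inputs from an unspecified FACT score. Under 0 to 4 item scoring, and on the size of the SD, those inputs appear to describe a domain of about seven items. This is a strong inference and not a proven fact, because the scoring is not in the document. The consequence is that 80% power with 102 patients is not shown for the stated endpoint.

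No single corrected power or sample size can be given, because the protocol has no SD or relevant difference for the total. With 3.0 points kept and four equal domain SDs of 5.4 assumed, power is about 28% to 11% and the detectable difference about 6.1 to 12.1 points as the correlation runs from 0 to 1. With a relevant difference of about 0.556 SD, power remains near 80%. Which of these applies is what the protocol needs to settle.

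**What to change.** Keep the FACT-G total as the primary outcome and say explicitly, in both Outcome measures and Sample size, that the total is the score analysed. State its range. Replace 22.7, 5.4 and 3.0 with the mean, SD and relevant difference for the total, and give the source of the relevant difference. The SD can come from the pooled month 0 FACT-G data, without splitting by arm. Then restate the power, or the difference detectable with 80% power, at the planned size. Do this before any unblinded outcome is seen.

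If the present figures do describe the total on some other scoring, stating that scoring and its range closes the point without recalculation.

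The cost is a change of wording and one recalculation from data already being collected. The downside is that the restated power or detectable difference may be less favourable than the one now given.

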**Methods:**

The trial is a multicentre, two-arm randomised controlled study. Patients are randomised parallel in either 'usual care' plus case management or 'usual care' alone. Patients with all types of cancer can be included in the study, if they have completed the therapy with chemo- and/or radiotherapy/surgery with curative intention and are expected to have a survival time >1 year. To determine the health-related quality of life the general questionnaire FACT G is used. The direct correlation between self-management and perceived self-efficacy is measured with the Jerusalem & Schwarzer questionnaire. Patients satisfaction with the care received is measured using the Patient Assessment of Chronic Illness Care 5 As (PACIC-5A). Data are collected at the beginning of the trial and after 3, 6 and 12 months. The power analysis revealed a sample size of 102 patients. The recruitment of the centres began in 2009. The inclusion of patients began in May 2010.

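### The 30% drop-out allowance multiplies 102 by 1.3 instead of dividing by 0.70, so 132 enrolled gives about 76% power, not 80%

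*Protocol article*

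**What the plan says.** All the inputs are in the Sample size section of the protocol article.

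- Target difference: "a variation of 3.0 units in the FACT-score is considered clinically relevant and is thus imputed as minimal difference (effect) to be achieved".
- Spread: "The standard deviation of FACT is 5.4 according to literature".
- Error rates: "the level of significance was set at 0.05, also a power at 0.8".
- Result: "The power analysis revealed a sample size of 102 patients". The same sentence appears in the abstract and in the Sample size section.
- Drop-out and enrolment: "Assuming a drop-out rate of 30% due to the severely ill patient population, 132 patients would need to be enrolled".

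Neither the sidedness of the test nor the allocation ratio is written out. The Randomisation section says "Treatment allocation will be done by random permutation within blocks with block sizes of 2 and 4", which, with two parallel arms, points to 1:1. The article gives no second drop-out rate, no rule for replacing missing outcomes and no other enrolment target.

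**The concern.** The 102 is the number of patients who must contribute a primary outcome for the stated power. The 132 has one purpose: to leave 102 after 30% of those enrolled are lost. It does not, because 70% of 132 is about 92. The slip is a common one: the drop-out percentage is applied to the number needed at the end instead of to the number who start.

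At stake is the accuracy of the planning statement. Anyone relying on 132 enrolled, 30% drop-out and 80% power is relying on three figures that are not compatible.

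**Working it through.** **Inputs** (Sample size section): difference δ = 3.0; SD σ = 5.4; α = 0.05; power 0.80; drop-out 30%. Assumed because not stated: two-sided test and 1:1 allocation.

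**1. Reproduce the 102.**

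n per arm = 2 × ((1.960 + 0.842) × 5.4 / 3.0)² = 50.9, so 51 per arm and 102 in total.

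This is an exact match. A one-sided test would give 82 in total, so the match supports the two-sided reading. It also shows that 102 contains no drop-out allowance.

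**2. Reproduce the 132.**

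| Inflation rule | Calculation | Result |
|---|---|---|
| Multiply by (1 + drop-out) | 102 × 1.30 | 132.6, stated as 132 |
| Divide by (1 − drop-out) | 102 / 0.70 | 145.7, so 146 |

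Only the first rule gives the plan's figure. Rounding explains 132 versus 133; it does not explain 132 versus 146.

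**3. Patients left after 30% drop-out.**

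- 132 × 0.70 = 92.4, about 46 per arm.
- 146 × 0.70 = 102.2.
- Shortfall in enrolment: 146 − 132 = 14.

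**4. Power at 92 evaluable.** Normal approximation, the method that reproduces the 102:

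power = Φ( δ / (σ × √(2/n)) − 1.960 )

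- n = 51: σ√(2/51) = 1.069; 3.0 / 1.069 = 2.805; Φ(0.845) = 0.801.
- n = 46: σ√(2/46) = 1.126; 3.0 / 1.126 = 2.664; Φ(0.704) = 0.759.

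| Evaluable | Normal approximation | t-test |
|---|---|---|
| 102 | 80.1% | 79.3% |
| 92 | 75.9% | 75.0% |

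The loss is about 4 percentage points on either method.

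**5. Drop-out that 132 can absorb.**

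1 − 102/132 = 0.227. So 132 preserves 102 evaluable patients only if drop-out is no more than 22.7%. Rounding this to 23% slightly overshoots, since 132 × 0.77 = 101.6.

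**6. Keep to one method.** By t-test, 80% needs 104 evaluable (52 per arm), which changes the tolerable drop-out to 1 − 104/132 = 21.2% and the enrolment to 104 / 0.70 = 148.6, so 149. The 76%, 22.7% and 146 belong together, because they rest on the method that gives the plan's own 102.

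**The case against.** The best case on the other side is about size. A drop from about 80% to 76% is what an SD of 5.69 instead of 5.4 would cause with all 102 patients retained (5.4 × √(102/92) = 5.69). That is a 5% error in a value taken from the literature, well within the uncertainty of most planning SDs. Allocation, endpoint and type I error are untouched. This stands, and it limits the point to the correction of a stated figure.

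One could also say that the 30% was meant as a share of the 102. But the implied drop-out rate is then 22.7%, and the text would have to say so. Nor can an analysis plan or fuller protocol resolve this, because the disagreement is between figures that the article itself states.

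Drop-outs might still supply some data, since questionnaires are also collected at 3 and 6 months. The primary goal, however, concerns quality of life at one year, patients who relapse or progress leave the study, and the sample size paragraph takes no credit for partial data. Assuming no 12-month outcome from drop-outs is reasonable, but it is an assumption.

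Three stronger readings are tempting, and the document does not support them:

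- *The abstract misreports the sample size.* It gives 102 as the result of the power analysis, which is true and agrees with the Sample size section. Leaving out the enrolment target is ordinary condensation.
- *A null result would be over-read.* Nothing in the article ties interpretation to the planned 80%, and a 4-point change would hardly alter how a confidence interval is read.
- *Baseline adjustment would recover the loss.* That needs 1 − r² = 92/102, a correlation between baseline and 12 months of about 0.31. The document gives no correlation, so the claim cannot be made from it.

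**Conclusion.** The enrolment figure is wrong on the plan's own assumptions. With 132 enrolled and 30% drop-out, about 92 patients are evaluable and power for a 3.0-point difference is about 76% (75% by t-test), not 80%. The target that matches the stated drop-out and power is 146, which is 14 more than stated.

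The result rests on a two-sided test and 1:1 allocation, both supported by the exact match at 102, and on equal drop-out between arms with no 12-month data from drop-outs. It takes the plan's difference and SD as given.

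The shortfall is modest. A reader might infer that the trial is seriously underpowered; a loss of about 4 points does not support that.

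**What to change.** Replace the drop-out sentence in the Sample size section with figures that agree, for example:

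> 132 enrolled with 30% drop-out gives about 92 evaluable patients and about 76% power for a 3.0-point difference; 80% power holds only if drop-out does not exceed 22.7%; keeping 80% power at 30% drop-out would correspond to 146 enrolled.

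State alongside it that the test is two-sided, allocation is 1:1, the normal approximation is used, drop-out is taken as equal between arms, and drop-outs are assumed to give no 12-month data.

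If the power is restated, the cost is one or two sentences and no change to the design. Fourteen more patients are needed only if the sponsor wants to keep both the 80% and the 30%. The abstract needs no change.
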